### **1.2 Secondary objectives**

Secondary objectives include the following.

- Incidence of malnutrition

Determine the efficacy of 14 days MNP supplementation versus a control group and RUTF versus MNP on the incidence of acute malnutrition during 6 months follow-up,

- Frequency of morbidity

Determine the effect of 14 days supplementation on the frequency of morbidity (3 study diseases) during 6 months follow-up, comparing both intervention groups to the control group and comparing RUTF to MNP)

- Weight changes immediately after intervention period, measured at day-14 and day-28

Measure mean weight change (total change and rate (grams/kg/day) of change), comparing both intervention groups separately (RUTF and MNP) to the control group

Determine frequency of 'no weight gain and/or weight loss', comparing both intervention groups separately (RUTF and MNP) to the control group

Assess if provision of 14 days of RUTF or MNP supplement promotes a sustained weight gain, measured after 28-days of follow-up, comparing both intervention groups separately (RUTF and MNP) to the control group

- Evaluation of several subgroup to assess potential effect modifiers.

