## **2 Study design**

This is a partially blinded randomized controlled trial with three study groups. Children 6 to 59 months of age presenting at the OPD in Goronyo and diagnosed with one or more of the three study diseases (malaria, diarrhoea and LRTI) are eligible for the study.

Children participating in this study will be randomised to one of 3 study groups to:

- A) Receive 14 days of RUTF supplementation with standard care and treatment or
- B) Receive 14 days MNP supplementation with standard care and treatment or
- C) Be included in a control group receiving standard care and treatment but not receiving nutritional supplementation (control group)

Individual follow-up will be 6 months. During this time, children in the RUTF or MNP group will receive 14 days nutritional supplement every time diagnosed with at least one of the three study diseases, not exceeding more than 14 days supplementation in any 28 day period.

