### 5.3 Primary analysis of primary endpoint

The primary endpoint is “negative nutritional outcome” of a child within the 6 months follow-up period. The incidence rate (in formulae below referred to simply as ‘rate’) of “negative nutritional outcome” will be computed as the number of events divided by total observed person-time in each treatment group. As an “event” the first time a child reaches a negative nutritional outcome will be used. The primary analysis of the primary endpoint will be performed on the intention to treat population with no imputation of missing data.

In the primary analysis, RUTF will be compared to the control group

The hypotheses in this step are

$$H_0: \text{rate}_{\text{RUTF}} = \text{rate}_{\text{Control}}$$

vs.

$$H_1: \text{rate}_{\text{RUTF}} \neq \text{rate}_{\text{Control}}$$

where  $\text{rate}_{\text{RUTF}}$  = rate of “negative nutritional outcome” in the children in the RUTF group, and  $\text{rate}_{\text{Control}}$  = rate of “negative nutritional outcome” in the children in the control group.

The comparison of rates among the two treatment groups (RUTF vs. control) will be performed by a Poisson regression model, adjusted for nutritional status at enrolment (fixed effect) and will be performed within one model including the three intervention groups with contrasts for each two-group comparison. The result will be presented as rates for each intervention group, and a rate ratio for the pair-wise comparison (each with 95% confidence intervals). Tests will be two-sided with a significance level of 0.05.

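### The primary Poisson model has no term for time since enrolment, so its RUTF-control rate ratio is biased if the NNO rate changes over the 6 months and loss also differs by arm

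*SAP*

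**What the plan says.** Section 5.3 of the SAP computes one rate per arm: it "will be computed as the number of events divided by total observed person-time in each treatment group". Only the first NNO counts: "As an “event” the first time a child reaches a negative nutritional outcome will be used". The RUTF-control comparison "will be performed by a Poisson regression model, adjusted for nutritional status at enrolment (fixed effect"). No term for time since enrolment is listed, and no check of a constant rate is planned. On the test, the section states: "Tests will be two-sided with a significance level of 0.05". The analysis "will be performed on the intention to treat population with no imputation of missing data".

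Section 2 sets the time frame: "Individual follow-up will be 6 months". Section 5.4.1 and the text that follows it use the same model for the later steps of the hierarchy, which opens only if the RUTF-control test is significant.

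Three other places touch the issue:
- Section 5.4.4 leaves any imputation, as a sensitivity analysis, to a decision after a blinded look at the missing data.
- Section 3.2 lists time to NNO as a secondary endpoint.
- Section 5.5 includes a Cox model among the methods for secondary endpoints, with explorative p-values.

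**The concern.** Events over total person-time weight every child-month equally. A person-time denominator is meant to absorb unequal follow-up, but it does so without bias only when the rate is the same in every child-month. If the rate varies, an arm that loses more children early has its person-time concentrated in the early period, and its overall rate moves towards the early rate. The arms then differ in rate because their follow-up differs, not because of treatment. Loss need not be related to NNO for this to happen.

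Both conditions are plausible here. Children enter with an acute illness and are supplemented in 14-day courses, so a flat rate over 6 months would be surprising. Weight is also examined early ("Weight changes immediately after intervention period, measured at day-14 and day-28"), which may affect when NNO is detected. Blinding is partial and one arm receives no supplement, so retention may differ.

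At stake is the one confirmatory test that opens the rest of the hierarchy.

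**Working it through.** The SAP states no NNO risk, time course, loss or sample size, so there is no figure to reproduce. All rates, losses and arm sizes below are assumptions.

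**Expected ratio, no true effect, loss at month 1.** Let the monthly rate be h1 = 0.09 in month 1 and h2 = 0.03 in months 2 to 6 (3-fold). A fraction d of the children still at risk is lost at month 1, independently of NNO. Per child:
- Month 1: events = 1 − exp(−0.09) = 0.0861; person-months = 0.0861 / 0.09 = 0.956.
- Later: events = (1 − d) × exp(−0.09) × (1 − exp(−0.15)) = (1 − d) × 0.1273; person-months = that / 0.03 = (1 − d) × 4.243.

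| Loss d | Events | Person-months | Rate | RUTF (5% lost) / control |
|---|---|---|---|---|
| 5% | 0.2070 | 4.988 | 0.0415 | – |
| 15% | 0.1943 | 4.563 | 0.0426 | 0.975 |
| 20% | 0.1879 | 4.351 | 0.0432 | 0.961 |
| 30% | 0.1752 | 3.927 | 0.0446 | 0.930 |

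With h1 = h2 the rate is 0.03 whatever d is, so the ratio is exactly 1.000. With equal d in both arms the ratio is also 1.000.

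**Dependence on the rate pattern and the timing of loss.** RUTF loses 5% throughout. Even loss means loss spread linearly over the 6 months, integrated numerically.

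| Month-1 rate vs later | Control loss | All at month 1 | Even over 6 months |
|---|---|---|---|
| 2-fold | 15% | 0.985 | 0.993 |
| 2-fold | 30% | 0.959 | 0.982 |
| 3-fold | 15% | 0.975 | 0.988 |
| 3-fold | 30% | 0.930 | 0.969 |
| 4-fold | 15% | 0.967 | 0.984 |
| 4-fold | 30% | 0.910 | 0.959 |

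Spreading the loss evenly roughly halves the bias.

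**Direction.** Swapping which arm loses more reverses the sign. So does a late peak. With a rate 2 to 4 times higher after month 3, a 6-month risk of 20% and loss over the first 3 months, the ratio is 1.010-1.019 for 15% (control) vs 5% (RUTF) lost and 1.025-1.046 for 30% vs 10%.

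**Type I error.** Simulation with a 3-fold early rate, loss at month 1, 700 per arm and a two-sided Wald test at 0.05. Ranges cover repeated sets of runs.

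| Loss RUTF / control | Planned model | With interval (month 1, later) |
|---|---|---|
| Equal | about 5.6% | about 5% |
| 5% / 15% | 6.0-6.5% | 4.7-5.4% |
| 5% / 20% | 7.0-7.3% | 4.7-5.4% |
| 5% / 30% | 9.4-10.0% | 4.7-5.4% |

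The 0.6-point excess with equal loss arises because the model-based standard error also assumes a constant rate. It is not caused by unequal loss.

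**With a true ratio of 0.70** (4-fold early rate, 20% control risk at 6 months, 700 per arm), the planned model gives 0.683 when 15% (control) vs 5% (RUTF) are lost early and 0.664 for 30% vs 10%. The split model gives 0.701 and 0.700. When loss is equal but the rate varies, a true 0.70 moves only to between 0.689 and 0.705.

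**The case against.** A reader might infer that unequal early loss is enough to bias the result. It is not: at a constant rate the ratio is exactly 1.000 even at 5% vs 30% loss. The SAP neither states nor excludes a changing rate.

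A reader might also infer that the bias favours RUTF. That needs both an early peak and heavier early loss in the control arm, and the SAP establishes neither. Children are treated at entry. For moderately malnourished children, NNO requires progression to severe malnourishment or a loss of at least 10% of a weight taken while ill, which does not clearly point to an early peak.

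The largest error rates need severe assumptions. Around 15% requires a 25-point loss gap falling entirely at month 1, a 3-fold rate drop at the same moment, and 1500 children per arm. None of these is in the SAP.

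Finally, the plan has partial cover. Time to NNO is prespecified, and Cox is the only time-to-event method listed for it. The review in section 5.4.4 looks at the timing of missing data, and an imputation that completed follow-up could remove the bias.

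The first three points stand and limit the claim. The last stands only in part: imputation is not committed, and the Cox analysis is explorative and not tied to the primary result.

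**Conclusion.** The concern holds in conditional form. The primary estimate and test rest on a constant NNO rate that the SAP neither justifies nor checks. If the rate changes over follow-up and loss differs by arm, the RUTF-control ratio is biased, in a direction that the document does not allow one to predict.

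For month-1 rates 2 to 4 times a later 0.03 per month, the shift is about 1-3% at a 10-point loss gap and 2-9% at a 25-point gap. The lower ends apply to evenly spread loss, the upper ends to loss at month 1. Type I error of about 6% to 9-10% rests on the 3-fold rate, loss at month 1 and 700 per arm. There is no bias at a constant rate, and none under no true effect with equal loss.

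The effect is modest unless the loss imbalance is large. The change is still worth making, because it protects the gateway test at little cost.

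**What to change.** In sections 5.3 and 5.4.1, split each child's time at risk into a few prespecified follow-up intervals, for example up to day 28 and later, with further cuts only where events are not sparse. Add interval as a factor in the same Poisson model and keep the rate ratio as the primary estimate. Also name the Cox model for time to NNO, adjusted for or stratified by nutritional status, as a sensitivity analysis of the primary result.

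The cost is SAP wording, one data-splitting step and a few extra model terms. The simulations used two intervals and no nutritional strata. They do not show how a model with many intervals crossed with nutritional status would behave, which is a reason to keep the intervals few.

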#### **3.2 Secondary endpoints**

Secondary endpoints include

- Number of NNO’s per study group in a period of 6 months
- Time to NNO
- Number of new events of a study disease in 6 months
- Weight change at 14 days and 28 days after study inclusion, and at end of study period
- Rate of weight change (grams/kg/day) at 14 days and 28 days after study inclusion, and at end of study period
- Proportion of children not gaining weight (including losing weight), measured at day-14 and day-28 after study inclusion.
- Proportion of children developing bilateral oedema, overall and per month
- Proportion of moderate acutely malnourished children improving to a non acutely malnourished state, overall and per month
- Mortality: overall mortality
- Morbidity, including the three study diseases (proportion of children with newly diagnosed diseases), overall and per month
- Proportion of children with a reported cough at clinical visit, overall and per month
- Proportion appetite categories
- Proportion and time pattern of children who were breast-fed at baseline and stopped being breast-fed during the study

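### The primary rate counts only first NNOs but divides by all observed person-time; no rule ends a child's time at the first NNO

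*SAP*

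**What the plan says.** Section 5.3 defines the primary incidence rate of NNO as "computed as the number of events divided by total observed person-time in each treatment group". For the event, "the first time a child reaches a negative nutritional outcome will be used", so each child contributes 0 or 1 to the numerator. RUTF is compared with control in a Poisson regression adjusted for nutritional status at enrolment, and the result is reported as rates and a rate ratio. "Tests will be two-sided with a significance level of 0.05". Neither the offset nor the variance estimator is stated.

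Three other places bear on how long a child is observed:

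- Section 2: "Individual follow-up will be 6 months", with no exit at an NNO.
- Section 3.2 lists "Number of NNO’s per study group in a period of 6 months" and weight change at the end of the study period. Both need data from after a first NNO.
- Section 4.3 defines completion by attendance at the first and last scheduled visits, whether or not an NNO has occurred.

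Section 3.1 describes the endpoint in a different way, as whether a child has any NNO during the 6 months.

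**The concern.** A first-event incidence rate needs a denominator that stops when the child can no longer have a first event. Section 5.3 stops the numerator there but not the denominator. A programmer who follows the sentence as written would sum all follow-up time, while another might truncate at the first NNO. The two would report different primary results from the same data.

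Under the literal reading, the arm with more events collects more surplus time, so its rate is understated more and the ratio is pulled towards 1. The event counts are unchanged, and with them the model-based standard error, so the test statistic shrinks.

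The sentence governs the primary test. Under section 5.4.1 a non-significant RUTF result makes all later comparisons exploratory. The same model serves steps ii and iii, and step iii sets its margin on an absolute difference in rates, so the meaning of that margin also depends on the denominator.

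**Working it through.** The SAP states no sample size, power, control rate or effect size, so there is no figure of its own to reproduce. The check uses assumed inputs.

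**From the SAP:** first event only; all observed person-time (literal reading); 6 months per child; two-sided 0.05; Poisson regression.

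**Assumed:** constant hazard, equal arms, no dropout, 6-month control risk p0 from 5% to 50%, true at-risk rate ratio 0.67. The covariate adjustment is left out.

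**Step 1: the ratio.** With 6 months as the unit of time, the hazards are h0 = −ln(1 − p0) and h1 = 0.67·h0, and p1 = 1 − exp(−h1). At-risk time gives h1/h0 = 0.67. Full follow-up time gives p1/p0, the risk ratio. At p0 = 20%: h0 = 0.2231, h1 = 0.1495, p1 = 0.1389, ratio 0.1389/0.20 = 0.694.

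Fixing the risks instead shows the same shift:
- 20% vs 14%: ln(0.86)/ln(0.80) = 0.676 at risk, 0.70 with full time.
- 30% vs 21%: ln(0.79)/ln(0.70) = 0.661 at risk, 0.70 with full time.

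**Step 2: the control rate.** Full time gives p0 in place of h0, a relative understatement of 1 − p0/h0. At 20% this is 1 − 0.20/0.2231 = 10%. It is 2.5% at 5% risk, 5% at 10%, 16% at 30%, 22% at 40% and 28% at 50%.

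**Step 3: power.** The number per arm is set for about 80% power with at-risk time: n = (1.96 + 0.84)²·(1/p0 + 1/p1)/(ln 0.67)². With d0 and d1 events, the model-based SE of the log ratio is √(1/d0 + 1/d1) under either denominator. With full time the count per child is binary, and the appropriate SE is the smaller √(1/d0 + 1/d1 − 2/n), which is what a robust variance estimates.

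At p0 = 20%, n = 598: model-based SE 0.143, robust SE 0.131, log ratio −0.365. Power with the model-based SE is Φ((0.365 − 1.96 × 0.143)/0.131), about 74%. Simulation gives 75%.

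**Step 4: type I error.** Under no difference, the model-based SE is too large by a factor 1/√(1 − p0). At 20% the effective critical value is 1.96/√0.80 = 2.19, a two-sided level of 0.028.

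Simulated results at a true ratio of 0.67 (40,000 trials per setting for full time, 3,000 for at-risk time):

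| Control risk | n per arm | Full-time ratio | Power, at-risk time | Power, full time, model SE | Type I, full time, model SE | Power, full time, robust SE |
|---|---|---|---|---|---|---|
| 5% | 2428 | 0.676 | 82% | 79% | 0.043 | 80% |
| 10% | 1208 | 0.682 | 81% | 78% | 0.039 | 81% |
| 20% | 598 | 0.694 | 80% | 75% | 0.028 | 81% |
| 30% | 394 | 0.709 | 80% | 71% | 0.019 | 80% |
| 40% | 292 | 0.725 | 80% | 65% | 0.012 | 80% |
| 50% | 230 | 0.743 | 81% | 57% | 0.005 | 80% |

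True ratios of 0.60 and 0.75 give the same pattern: the full-time ratio runs from 0.606 to 0.680 and from 0.755 to 0.811 as the control risk goes from 5% to 50%. Type I error with at-risk time, and with full time and a robust SE, stays near 0.05.

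**The case against.** The strongest reply is that the SAP never says post-event time is counted. In a first-event incidence rate, observed person-time can be read as time observed for that event, which is time at risk. Sections 2, 3.2 and 4.3 show that children stay under observation after an NNO; they do not say that this time enters the primary denominator. This stands. A reader might infer that the plan definitely uses post-event time, and the document does not support that. What remains is that the formula as worded includes it and nothing elsewhere excludes it.

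Second, the loss of power needs a model-based variance as well as the literal denominator. The SAP specifies no variance estimator, and with a robust one the loss largely disappears. This stands too, but a plain Poisson regression with no robust variance named would ordinarily be run with the model-based one.

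Third, section 3.1 compares children with and without any NNO in 6 months. With complete follow-up the literal ratio is a valid risk ratio for that comparison, so its distance from the at-risk ratio is a difference of estimand rather than plain bias. This is fair. However, section 5.3 promises an incidence rate and a rate ratio, and the risk-ratio reading needs complete and equal follow-up.

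Finally, one might see a contradiction with a Cox analysis of time to NNO. There is none: time to NNO is a separate secondary endpoint with exploratory p-values (section 5.5).

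**Conclusion.** The point holds as a mismatch between numerator and denominator in the primary rate. Applied literally, section 5.3 does not give the incidence rate it names: rates are understated and the ratio lies nearer 1. With a model-based variance the test of RUTF against control is also conservative.

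The size depends on the NNO risk, which the SAP does not give. On the assumptions above, the loss from a nominal 80% power is about 1 point at 5% control risk, 5 points at 20% and 23 points at 50%. A reader might infer that the trial is underpowered or its primary result invalid. The document supports neither: at low risk the effect is negligible, type I error of this test is not inflated, and a robust variance restores most of the power. The sentence still deserves correction, because it governs the primary, gatekeeping test and can be programmed in two ways.

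**What to change.** In section 5.3, define the primary rate as the number of first NNO events divided by person-time at risk, counted from enrolment to the earliest of first NNO, death, last contact or the 6-month visit. State that the log of this time is the Poisson offset. Keep all observed time for the secondary endpoint that counts every NNO.

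If full follow-up time is really intended, say so, call the result a risk ratio, and specify a robust variance; that reading also relies on complete follow-up.

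Either choice costs about one sentence in the SAP and needs no new data.

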### 5.4 Secondary analysis of the primary endpoint

#### 5.4.1 Treatment group comparisons

Although the study is primarily powered for the comparison between the RUTF and control group the other groups will be compared as well, keeping in mind that the sample size might not be large enough to obtain significant results.

Since there are three interventional groups to be compared, a hierarchical test procedure will be used to account for multiplicity.

i) In a first (primary) step, RUTF will be compared to the control group which is described above as analysis of primary outcome

If the RUTF group is not significantly different at a 0.05 level (two-sided test), the hierarchical procedure is stopped (all following analyses will be considered explorative). If the RUTF group is significantly different at a 0.05 level, the hierarchical procedure is continued with step 2.

ii) In the second step, MNP will be compared to the control group

The hypotheses in this step are

$$H_0: \text{rate}_{\text{MNP}} = \text{rate}_{\text{Control}}$$

vs.

$$H_1: \text{rate}_{\text{MNP}} \neq \text{rate}_{\text{Control}}$$

where  $\text{rate}_{\text{MNP}}$  = rate of “negative nutritional outcome” in the children in the MNP group, and  $\text{rate}_{\text{Control}}$  = rate of “negative nutritional outcome” in the children in the control group.

If the treatment factor is not significant at a 0.05 level (two-sided test), the hierarchical procedure is stopped (all following analyses will be considered explorative). If the treatment factor is significant at a 0.05 level, the hierarchical procedure is continued with step iii).

iii) In the third step, RUTF will be compared to MNP (non-inferiority test).

The hypotheses in this step are

$$H_0: \text{rate}_{\text{RUTF}} - \text{rate}_{\text{MNP}} > -\delta$$

vs.

$$H_1: \text{rate}_{\text{RUTF}} - \text{rate}_{\text{MNP}} \leq -\delta$$

where  $\text{rate}_{\text{RUTF}}$ =rate of “negative nutritional outcome” in the children in the RUTF group,  $\text{rate}_{\text{MNP}}$ =rate of “negative nutritional outcome” in the children in the MNP group, and  $\delta$ =inferiority margin.

As non-inferiority margin, a  $\delta$  of 2% (absolute value) will be used (i.e. allowing a slightly worse result in the MNP compared to the RUTF group). The third step will be tested at a 0.025 level (one-sided test), by a one-sided 97.5% confidence interval of the difference in rates between the RUTF and the MNP group.

The general problem of assay sensitivity in non-inferiority comparisons can be addressed in this study by the 3-arm design including a control group receiving no nutritional supplementation. Thus, superiority of the two nutritional interventions (RUTF and MNP) versus no intervention can be evaluated prior to the non-inferiority comparison.

These step-wise comparisons of rates among treatment groups will be performed by the same Poisson regression model, adjusted for nutritional status at enrolment (fixed effect) as described above, i.e. performed within one model including the three intervention groups with contrasts for each two-group comparison. The results will be presented as rates for each intervention group, and rate ratios for the pair-wise comparison (each with 95% confidence intervals).

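### The gates of steps i and ii in SAP 5.4.1 do not require benefit over control, and step ii names the treatment factor instead of the MNP-versus-control contrast

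*SAP*

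**What the plan says.** SAP 5.3 compares RUTF with control by Poisson regression and states: "Tests will be two-sided with a significance level of 0.05". SAP 5.4.1 makes this the first step of a hierarchy.

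- **Step i (RUTF versus control).** "If the RUTF group is significantly different at a 0.05 level, the hierarchical procedure is continued with step 2". Otherwise the procedure stops and what follows is exploratory.
- **Step ii (MNP versus control).** The comparison is introduced as "In the second step, MNP will be compared to the control group", with a null of equal rates in those two groups and an alternative of unequal rates. The stop rule is "If the treatment factor is not significant at a 0.05 level (two-sided test), the hierarchical procedure is stopped" and the continue rule is "If the treatment factor is significant at a 0.05 level, the hierarchical procedure is continued with step iii".
- **Step iii (RUTF versus MNP, non-inferiority).** One-sided 0.025 level, margin 2% absolute.

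The closing text of 5.4.1 says that the three-arm design answers the assay-sensitivity problem, because "superiority of the two nutritional interventions (RUTF and MNP) versus no intervention can be evaluated prior to the non-inferiority comparison". It adds that the step-wise comparisons are "performed within one model including the three intervention groups with contrasts for each two-group comparison".

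**The concern.** There are two separate faults in the gate rules.

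**Direction.** Both gates ask only whether a supplement differs from control. Neither asks whether its rate of negative nutritional outcome is lower. The stated reason for placing these gates before step iii is superiority of both supplements, and the rules do not require it. If both supplements were worse than control to a similar degree, the hierarchy as written would go on to a confirmatory claim that one is not inferior to the other. That is the situation an assay-sensitivity condition is meant to exclude.

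**Object of the step ii test.** Step i names the RUTF group. Step ii names the treatment factor. The only planned model holds all three groups, so its treatment factor has three levels, and the usual test of such a factor is a 2-df test of any difference among the arms. Step ii is reached only after RUTF has already differed from control, so a test of the whole factor would say little about MNP. The gate's wording therefore does not match the step's own hypothesis.

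**Working it through.** The SAP gives no sample size, event count, rate or power, so there is no design figure to reproduce. The levels and hypotheses below come from SAP 5.3 and 5.4.1. Power, event counts and rate ratios are assumptions and are marked as such.

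**1. What step ii tests, from the text.**

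| Feature of the SAP | Points to |
|---|---|
| Step ii introduced as MNP against control | 1-df contrast |
| Null and alternative contain only the MNP and control rates | 1-df contrast |
| Stop rule labelled as a two-sided test | 1-df contrast (a 2-df chi-square has no sides) |
| Contrasts for each two-group comparison | 1-df contrast |
| Gate sentences name the treatment factor in a three-group model | 2-df factor test |

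The weight of the text favours the contrast. Only the gate sentences themselves say otherwise.

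**2. Direction gap, contrast reading.** A gate opens if |z| > 1.960, with z = ln(rate ratio) / √(1/d₁ + 1/d₀), where d₁ and d₀ are the event counts. It opens on harm if z > 1.960.

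- No effect of either supplement: one gate opens on harm with probability 0.05/2 = 2.5%. Both open on harm in about 0.5% of trials; the shared control arm makes this larger than 0.025² = 0.06%.
- Assumed 100 control events and a true rate ratio of 1.5 for both supplements: expected z = ln 1.5 / √(1/150 + 1/100) = 0.405/0.129 = 3.14, so one gate opens on harm with probability about Φ(3.14 − 1.96) = 0.88. Simulation of Poisson counts (400,000 runs, equal person-time, no covariate) gives 0.89 for one gate and 0.81 for both.
- Same, with a true ratio of 1.25 for both: 0.38 for one gate and 0.23 for both.

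**3. What the literal wording would do.** Assume MNP equal to control and equal precision per arm, with normal log-rate estimates. The factor test is significant if the 2-df Wald statistic exceeds 5.991; the contrast is significant if |z| > 1.960. Results from 1,000,000 replicates, given that step i has passed:

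| Assumed power, RUTF versus control | 2-df factor significant | MNP-control contrast significant |
|---|---|---|
| 50% | 84% | 4–5% |
| 80% | 95% | 4–5% |
| 90% | 98% | 4–5% |
| 95% | 99% | 4–5% |

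At 80% power the probability of passing both steps is 0.80 × 0.95 = 0.76 under the factor test and 0.034 under the contrast. The Poisson simulation with 100 control events and a RUTF/control ratio of 0.67 gives 0.667 against 0.030. Over 50 to 200 control events, the factor test passes, given step i, in 67–86% of trials at ratio 0.8, 81–99% at 0.67 and 96–100% at 0.5.

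**4. Error level on the contrast reading.** With MNP equal to control, the contrast passes in 4.8–5.0% of trials, and steps i and ii both pass in 0.9–4.9% across the assumed scenarios. Adding the condition that MNP has the lower rate would bring the contrast's pass rate to about 2.5%.

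**The case against.** The strongest defence is that step ii is already a contrast. Its hypotheses, its two-sided label and the contrasts promised for each pair all say so, and the SAP nowhere mentions 2 df, an overall test or a three-group test. That stands. A reader might infer from the gate wording that the plan tests three groups jointly in step ii, and that the 76% figure describes this trial. The documents do not support that. The figure shows what would follow if the sentence were applied literally, and so why it should not be left as it is.

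A reader might also infer that the hierarchy fails to control the family-wise error rate. On the contrast reading it does not fail: a fixed sequence of contrasts, each at its full level, protects the stated nulls. Nor does the missing direction condition change this. If a supplement is truly harmful, the null of equality is false and rejecting it is no type I error.

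On direction, it is fair to say that a double harmful result is improbable under no effect, that the large probabilities need supplements assumed truly worse than control, and that the SAP reports group rates and rate ratios with 95% intervals, so harm would be visible. Many analysts also read the direction from the estimate after a two-sided test. These points limit the size of the problem. They do not supply the missing condition: as written, the rule still continues to step iii after a harmful result.

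**Conclusion.** The point holds in two parts.

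- **Direction.** The rules for steps i and ii do not require the superiority on which 5.4.1 bases assay sensitivity. This follows from the wording alone and holds on either reading of step ii. The probability that both gates open on harm is small under no effect (about 0.5%) and large only if both supplements are clearly harmful (81% at an assumed ratio of 1.5 with 100 control events).
- **Wording.** Step ii's gate names a three-level factor where its hypothesis concerns two groups. The contrast is the better-supported reading, so this is a wording defect and not a demonstrated 2-df test. The two readings give very different results under every non-null RUTF effect tried, so the choice should not remain open when the data are analysed.

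The primary RUTF-control analysis in 5.3 is unaffected. What depends on the correction is the confirmatory status of step iii and, only if the gate were applied literally, of step ii. Severity is low to moderate.

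**What to change.** Amend the stop and continue sentences of steps i and ii in SAP 5.4.1:

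- **Step i:** continue to step ii only if the RUTF-versus-control contrast is significant at two-sided 0.05 and the estimated rate ratio versus control is below 1. Otherwise stop, and treat later steps as exploratory.
- **Step ii:** replace the reference to the treatment factor by the MNP-versus-control contrast in both sentences. Continue to step iii only if that contrast is significant at two-sided 0.05 and the estimated rate ratio versus control is below 1. Otherwise stop.

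The two-sided tests and their reporting stay as planned, so a significant result in the harmful direction is still reported as such; it just no longer opens the next step. The cost is a wording change in one section. The planned model already yields these contrasts and rate ratios, so no new data or analysis is needed.
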